## 3.0 Study Design

### 3.1 Study summary

This will be a phase II, multicenter, randomized, double-masked, placebo-controlled study to assess the safety and efficacy of a standardized silymarin preparation (Legalon®) for treating patients with NASH, as defined by a NAS score of at least 4 on a baseline biopsy. Participating centers and Principal Investigators in the study are shown in Table 1. A total of 120 subjects will be enrolled at the 4 clinical centers. All subjects will be at least 18 years old, have serum AST or ALT  $>$  40 IU/L and demonstrated fatty liver. After careful evaluation, all eligible subjects will be entered into a 28-day lead-in phase in which they will undergo counseling with respect to diet, exercise, and alcohol consumption. Participants successfully completing the lead-in phase will be randomized to treatment with one of two dosages of Legalon® or a placebo. Legalon® will be administered orally thrice daily for 48-50 weeks. Subjects will be evaluated regularly for adverse events and for monitoring efficacy through blood sampling. After completing therapy, subjects will be monitored for an additional 12 weeks to measure any sustained effects of study medication and to continue to monitor for resolution of any adverse events.

### 3.2 Study Population

Participants will be at least 18 years old, have serum AST or ALT > 40 IU/L, and demonstrated fatty liver.

### 3.3 Entry Criteria

To be eligible for randomization, patients must meet all of the inclusion criteria and none of the exclusion criteria below:

#### Inclusion Criteria

- Age at least 18 years at the start of the lead-in period
- AST or ALT greater than 40 IU/L within one year of the start of the lead-in phase and at least once during the lead-in phase
- Successfully complete a 28-day lead-in phase. Successful completion of the lead-in phase will require the participant's BMI at the end of the lead-in period to be within +/- 10% of their BMI obtained at the initial lead-in visit, as well as adherence to the alcohol consumption guidelines.
- Have a liver biopsy performed within 18 days of completing the lead in phase demonstrating features consistent with NASH without cirrhosis; NAS score of at least 4.
- Negative urine pregnancy test (for women of childbearing potential) documented within the 24-hour period prior to the first dose of study medication. Females of childbearing

potential must be using two reliable forms of effective contraception during the study (while on study drug and during follow-up)

- Demonstrated fatty liver on an imaging modality, either ultrasound, CT, or MRI, within 1 year of the start of the lead-in phase
- Participant agrees to discontinue use of other antioxidants such as vitamin E, vitamin C, glutathione, alpha-tocopherol, or non-prescribed complementary alternative medications (including dietary supplements, megadose vitamins, herbal preparations, and special teas) from the start of the lead-in phase through completion of the follow-up phase. A multivitamin at standard doses will be allowed.
- Participant agrees to discontinue use of silymarin or other milk thistle preparations, other than study medication, from the start of the lead-in phase through completion of the follow-up phase

### Exclusion Criteria

- BMI  $\geq 45$  kg/m^2 between the first lead-in visit and randomization
- Type 2 diabetes treated with oral agents other than the secretagogues or metformin; these include, thiazolidinediones, alpha-glucosidase inhibitors, exenatide, pramlintide between the start of the lead-in phase and randomization. Januvia (sitagliptin) is allowed.
- Evidence of poorly-controlled diabetes (Hba1c > 8%) between the first lead-in visit and randomization
- Known allergy/sensitivity to milk thistle or its preparations
- Use of drugs associated with a clinical or histological picture consistent with fatty liver disease or NASH for more than 12 consecutive weeks in the 1 year prior to start of the lead-in phase; these include amiodarone, tamoxifen, methotrexate, glucocorticoids, anabolic steroids, tetracyclines, estrogens at doses greater than those used for hormone replacement, valproate/valproic acid
- For patients using antihyperlipidemic agents or accepted anti-diabetic agents, any change of agent or dose from the start of the lead-in phase through randomization
- Use of warfarin, metronidazole, or acetaminophen (greater than 2 grams per day) from the start of the lead-in phase through randomization
- Lactose intolerance defined as patient reported inability to tolerate milk products
- History of other chronic liver disease, including metabolic diseases, documented by appropriate test(s)
- Previous liver biopsy that demonstrated presence of cirrhosis
- Radiologic imaging consistent with cirrhosis and portal hypertension
- Clinical or histological evidence of cirrhosis or, in the opinion of the investigator, the inability to safely obtain a liver biopsy due to technical reasons, such as body habitus.
- Evidence of decompensated liver disease defined as any of the following: serum albumin <3.2 g/dl, total bilirubin > 1.5 mg/dl, or PT/INR > 1.3 times normal from the start of the lead-in phase through randomization, or history or presence of ascites or encephalopathy, or bleeding from esophageal varices
- Platelet count < 130,000/mm^3 at any time from the first lead-in visit through randomization
- Serum creatinine of 2.0 mg/dL or greater or CrCl  $\leq 60$ cc/min, or on dialysis, at any time from the first lead-in visit through randomization. The creatinine clearance (CrCl) will be calculated according to Cockcroft-Gault.

### 3.4 Study Treatment

Participants will be randomized to treatment with either Legalon® 420 mg or 700 mg, or placebo administered thrice daily. The treatment period will be for 48-50 weeks and subjects will be followed off treatment for an additional 12 weeks. An IND (#74887) has been filed for the use of Legalon® in this study and a dossier reflecting additional preclinical and clinical information about this agent accompanies this protocol (Appendix 3).

Each patient will receive 5 capsules as outlined in Table 2 for each orally administered dose that will consist of Legalon® and/or placebo in the appropriate capsule quantities to standardize pill burden, allow for an estimate of compliance, and to minimize the potential for variable absorption due to differential solubility in the gastrointestinal tract.

Legalon® (Rottapharm/Madaus) is a milk thistle fruit extract standardized to 140 mg silymarin per capsule (53% as total silybins). A Legalon® 140 capsule contains 180 mg dried extract of milk thistle fruits, or 140 mg silymarin which is the presumed active ingredients, or 108 mg silymarin quantitated as silybin by HPLC. The total weight of the capsule is 429 mg and includes: other milk thistle components that are not chemically well defined; components of the extraction process; excipients; and the capsule shell. The 108 mg of silymarin in Legalon® 140 capsules consists of the following potentially active ingredients: silybins A + B (~50 mg), silychristin (~20 mg), silydianin (~15mg), and isosilybins A + B (~15 mg).

**Table 2**  
**Dosing Strategy for Standardizing Pill Burden**

| Legalon® Dose | # Legalon® Caps | # Placebo Caps | Total # of Capsules per Dose |
|---------------|-----------------|----------------|------------------------------|
| Placebo       | 0               | 5              | 5                            |

|        |   |   |   |
|--------|---|---|---|
| 420 mg | 3 | 2 | 5 |
| 700 mg | 5 | 0 | 5 |

### 3.4.1 Dose Adjustment Guidelines

Specific dose adjustment guidelines are provided to investigators for adverse effects considered to be possibly related to silymarin, including laboratory abnormalities, adverse events, and vital signs changes, investigators should utilize the "General Dose Reduction Guidelines" (Section 3.4.2) below. When practical, abnormal laboratory results should be confirmed as soon as possible following notification of the investigator. If appropriate, downward adjustments in one level increment (see below) should be considered.

### 3.4.2 General Dose Reduction Guidelines

Dose reduction for adverse events will be based upon severity ratings in accordance with Common Toxicity Criteria for Adverse Events (CTCAE) (Appendix 4). For grade 1 toxicity, no dose reduction is needed. For toxicity grade 2 that persists over two consecutive safety visits and is not responsive to adjunctive symptomatic management, a level 1 dose decrease of study medication may occur at the discretion of the investigator. For toxicity grade 3 not responsive to adjunctive measures, a level 1 dose decrease of study medication is required. Subjects with grade 3 toxicity should be followed closely, possibly at more frequent intervals or via telephone contact to monitor in between regularly scheduled safety visits. If symptoms improve, return to previous dosing is allowed at the discretion of the investigator. For grade 4 toxicities, treatment will be discontinued. It should be noted that certain toxicities carry different levels of significance for each patient and therefore, the investigator should use these as guidelines only, within the context of clinical judgment.

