## 2.3 Endpoints

**Efficacy:** The primary outcome variable (endpoint) for efficacy is improvement by at least 2 points in histology (NAS).

**Safety:** The primary outcome variable for safety is the occurrence of a dose-limiting toxicity during the 48-50 week treatment period. Adverse events (AE) will be categorized by severity.

**Adherence:** Will be measured using a summary of missed dose information obtained from patient diaries and dose counts and will be analyzed as both an outcome and as an explanatory variable in exploratory analyses of pharmacokinetic exposure and response.

**Biomarkers:** The following relationships will be explored: dose and change in biomarkers, changes in biomarkers and treatment success, changes in biomarkers and toxicity.

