### 3.4.3 Dose-Specific Reduction Guidelines

#### Dose Reduction Guideline – Silymarin 700 mg dose level

| AE Grade         | Reduction? | Discontinue? | Silymarin | Placebo | Pill Burden |
|------------------|------------|--------------|-----------|---------|-------------|
| Mild             | No         | No           | 5         | 0       | 5           |
| Moderate*        | Yes        | No           | 4         | 1       | 5           |
| Severe**         | Yes        | Temp         | 3         | 2       | 5           |
| Life Threatening | No         | Yes          | 0         | 0       | 0           |

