#### Dose Reduction Guideline – Silymarin 420 mg dose level

| AE Grade         | Reduction? | Discontinue? | Silymarin | Placebo | Pill Burden |
|------------------|------------|--------------|-----------|---------|-------------|
| Mild             | No         | No           | 3         | 2       | 5           |
| Moderate*        | Yes        | No           | 2         | 3       | 5           |
| Severe**         | Yes        | Temp         | 1         | 4       | 5           |
| Life Threatening | No         | Yes          | 0         | 0       | 0           |

\*\*Severe AE: Discontinuation for 1 week. If SAE improves or resolves, restart at indicated dose level at the investigator's discretion. The dose level may be increased to original dose level at the discretion of the investigator with continued close monitoring.

\*Moderate AE: Patient can resume original dose level if AE improves or resolves. NOTE: If the subject experiences a drug related AE and two dose reductions are not tolerated, the subject will stop the drug

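### For grade 2 and grade 3 toxicity, Protocol Sections 3.4.2 and 3.4.3 give different dose-reduction instructions, and the size of a dose level is never defined

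*Protocol*

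**What the plan says.** **Section 3.4.1** sends investigators to Section 3.4.2 for effects possibly related to silymarin. It speaks of stepping down one level at a time without saying how large a level is.

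**Section 3.4.2** works by CTCAE grade. Grade 1 needs no reduction and grade 4 ends treatment. For grade 2 the condition is "For toxicity grade 2 that persists over two consecutive safety visits and is not responsive to adjunctive symptomatic management", and the action is that "a level 1 dose decrease of study medication may occur at the discretion of the investigator". For grade 3: "For toxicity grade 3 not responsive to adjunctive measures, a level 1 dose decrease of study medication is required". Nothing is said about interrupting the drug. The section closes by describing its contents as guidance to be applied with clinical judgement.

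**Section 3.4.3** has one table per active dose, the first headed "Silymarin 700 mg dose level". Each has rows for mild, moderate, severe and life-threatening events. In the 700 mg table the moderate row reads "Moderate* | Yes | No | 4 | 1 | 5": reduction yes, no discontinuation, four active capsules and one placebo. The severe row gives reduction yes, temporary discontinuation and three active capsules. The corresponding rows of the 420 mg table give two and one active capsules. The footnote says "Severe AE: Discontinuation for 1 week", followed by a restart at the row's capsule count, at the investigator's discretion, if the event improves. A further note stops the drug when two reductions for a drug-related event have not been tolerated.

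**The concern.** Two adjacent sections tell an investigator what to do for the same grade of toxicity. At grade 3 they differ on when to act, on how far to reduce and, on their face, on whether to interrupt. At grade 2 they differ on whether reduction is optional and on what triggers it. No sentence says which section takes precedence.

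This matters because the protocol relies on these rules. The dose-selection rationale accepts that free silymarin exposure at 700 mg could be substantially higher than anything seen in Phase I. It names dose reduction or discontinuation under Section 3.4.1 as part of the protection, and Section 3.4.1 leads straight to the text that the tables do not match. At stake are how patients with moderate or severe toxicity are handled, how much drug they receive afterwards, and whether the two-reductions stopping note can be applied in the same way everywhere.

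**Working it through.** **No figure in the plan is disputed.** The one stated figure tied to toxicity is the 12% power in Section 6.1 (rates 0.05, 0.10, 0.10; 40 per arm; alpha 0.05). The mean rate is 0.25/3 = 0.0833. The noncentrality is 40 × [(0.05 − 0.0833)² + 2 × (0.10 − 0.0833)²] / (0.0833 × 0.9167) = 0.87 on 2 df, which gives power 12.1%. It reproduces and is unaffected by this point.

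**Text and tables side by side** (mild to life-threatening taken as CTCAE grades 1 to 4; the tables' first column is headed as the AE grade):

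| Grade | Section 3.4.2 | Section 3.4.3 | Agree? |
|---|---|---|---|
| 1 | No reduction | No reduction | Yes |
| 2 | Level 1 decrease, optional, after persistence and non-response | Reduction yes; 5 to 4 or 3 to 2 capsules; no condition | Ambiguous |
| 3 | Level 1 decrease, required if unresponsive; silent on interruption | One week off, then 5 to 3 or 3 to 1 capsules; no non-response condition | No |
| 4 | Discontinue | Discontinue | Yes |

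**Can one meaning of a level reconcile them?** The text uses the same level 1 step for grades 2 and 3.
- If a level is one capsule, grade 2 matches the moderate rows (5 to 4, 3 to 2). Grade 3 under the text would be 5 to 4 or 3 to 2, against 5 to 3 or 3 to 1 in the severe rows.
- If a level is two capsules, grade 3 restart doses match. Grade 2 under the text would be 5 to 3 or 3 to 1, against 5 to 4 or 3 to 2 in the moderate rows.

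Neither value fits both rows, and the one-week stop appears only in Section 3.4.3 under either. Section 3.4.3 does not settle the term: its table titles use dose level for the arm's assigned dose, and its footnote uses it for the dose in a row.

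**Size for one grade 3 event**, assuming a level is one capsule. Inputs: 140 mg per capsule (Section 3.4), three doses a day. Daily dose = capsules × 140 × 3.
- 700 mg arm, text: 4 × 140 = 560 mg per dose, 1,680 mg/day, a 20% cut, no break stated.
- 700 mg arm, tables: 7 days at zero, then 3 × 140 = 420 mg per dose, 1,260 mg/day, a 40% cut. Three active plus two placebo capsules is the low-dose regimen of Table 2.
- 420 mg arm, text: 2 × 140 = 280 mg per dose, 840 mg/day, a 33% cut.
- 420 mg arm, tables: 7 days at zero, then 140 mg per dose, 420 mg/day, a 67% cut.

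Over the first 28 days, with no return to a higher dose:
- 700 mg arm: text 1,680 × 28 = 47,040 mg; tables 1,260 × 21 = 26,460 mg; 1 − 26,460/47,040 = 44% less.
- 420 mg arm: text 840 × 28 = 23,520 mg; tables 420 × 21 = 8,820 mg; 1 − 8,820/23,520 = 63% less.

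**The stopping note.** It counts two reductions. Whether a direct move from 5 to 3 capsules counts as one or two depends on the undefined step.

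**The case against.** Several points on the other side have force.

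- *The sections can be read as complementary.* Section 3.4.2 would supply the trigger and Section 3.4.3 the capsule count. For grade 2 this works reasonably well, so ambiguity is the fair word there. For grade 3 it fails on step size, because the text assigns the step it also gives to grade 2 and the tables assign a larger one.
- *Silence is not prohibition.* Section 3.4.2 does not exclude an interruption, and the footnote could be read as adding one. That is fair. The firm grade 3 conflict is the step size, together with a non-response condition that only the text contains.
- *These are guidelines.* Both sections allow a return to the earlier dose, and some variation in handling would survive any redraft. But the grade 3 step is worded as a requirement, and clinical judgement does not explain two different defaults.

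Two stronger readings are tempting and should not be adopted.

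- A reader might infer that the primary safety endpoint inherits the conflict. Section 2.3 says "The primary outcome variable for safety is the occurrence of a dose-limiting toxicity during the 48-50 week treatment period", but the protocol does not define that term and nothing ties it to Sections 3.4.2 or 3.4.3. If it is defined by grade alone, the link is weak. It is a possible consequence, no more.
- A reader might infer that toxicity rates can no longer be compared between arms. Section 6.0 allocates within site and diabetes strata, treatment is double-masked, and every arm takes five capsules per dose. A site following either section applies it, masked, to all its arms, so differing site practice does not by itself favour an arm. Section 6.1 also says that the three-arm toxicity test is not a primary hypothesis.

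**Conclusion.** The protocol is wrong as written for grade 3 and at least ambiguous for grade 2; grades 1 and 4 are consistent. No single capsule value of a level satisfies both the text and the tables, no precedence is given, and the dose-selection rationale relies on these reductions as a safeguard at 700 mg.

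Per grade 3 event in the 700 mg arm, the difference is a one-week stop plus 140 mg per dose (560 against 420 mg), or 420 mg/day after restart. That size assumes one level is one capsule. If a level were two capsules, the mismatch in dose would move to grade 2 and the one-week stop would still appear only in the tables. The 28-day totals also assume no return to a higher dose. The number of patients affected cannot be computed, because the protocol gives no grade 2 or grade 3 event rate. No sample size, power or alpha figure changes.

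**What to change.** Reconcile Sections 3.4.2 and 3.4.3 for grades 2 and 3 into one rule per CTCAE grade. Each rule should state the trigger, whether reduction is required or optional, whether dosing is interrupted, and the number of capsules. The clinical team decides which passage stands; this review takes no position on that.

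Define a level in capsules, and say how a direct move to the severe row counts towards the two-reductions stopping note. In the footnote to the tables, replace SAE with severe AE, since Section 7.5 uses the abbreviation for serious events; this is editorial.

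The cost is a protocol clarification and a notice to the four sites. Nothing in the statistical design has to change.

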### 3.4.3 Dose-Specific Reduction Guidelines

#### Dose Reduction Guideline – Silymarin 700 mg dose level

| AE Grade         | Reduction? | Discontinue? | Silymarin | Placebo | Pill Burden |
|------------------|------------|--------------|-----------|---------|-------------|
| Mild             | No         | No           | 5         | 0       | 5           |
| Moderate*        | Yes        | No           | 4         | 1       | 5           |
| Severe**         | Yes        | Temp         | 3         | 2       | 5           |
| Life Threatening | No         | Yes          | 0         | 0       | 0           |

#### Dose Reduction Guideline – Silymarin 420 mg dose level

| AE Grade         | Reduction? | Discontinue? | Silymarin | Placebo | Pill Burden |
|------------------|------------|--------------|-----------|---------|-------------|
| Mild             | No         | No           | 3         | 2       | 5           |
| Moderate*        | Yes        | No           | 2         | 3       | 5           |
| Severe**         | Yes        | Temp         | 1         | 4       | 5           |
| Life Threatening | No         | Yes          | 0         | 0       | 0           |

\*\*Severe AE: Discontinuation for 1 week. If SAE improves or resolves, restart at indicated dose level at the investigator's discretion. The dose level may be increased to original dose level at the discretion of the investigator with continued close monitoring.

\*Moderate AE: Patient can resume original dose level if AE improves or resolves. NOTE: If the subject experiences a drug related AE and two dose reductions are not tolerated, the subject will stop the drug

### **3.4.4 Safety measurements**

#### Laboratory evaluations

Participants will undergo laboratory tests according to the time and event schedule to monitor for medication toxicities.

#### Pharmacokinetic Safety Monitoring

Blood samples will be collected and processed at each site and then shipped to the NIDDK repository. Aliquots needed for PK testing will be shipped to the central analytical lab at UNC. .Treatment week 2 samples from the first 6 patients receiving the highest dose (700 mg three times per day) will be used for bioanalysis to determine the range of  $\Sigma$  Free silymarin concentrations. Depending on the results, the determination of testing blood samples obtained from subsequent subjects will be made.

#### Adverse event monitoring

Participants will be queried by study personnel at each study visit about the incidence of adverse events. These will be documented in the study record and classified according to duration, severity, relationship to study medication, and action with study medication. Serious adverse events will be reported to appropriate regulatory authorities, in addition to the DSMB as below, in a timely fashion.

In the event that an investigator considers an adverse event to be related to study medication, the investigator may submit an unmask request to the clinical center investigational pharmacist to unmask the study drug dose, per the study specific unmasking procedure.

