### **3.5 Premature discontinuation**

Treatment may be discontinued prematurely for the following reasons:

1. Participant requests termination of the study medication
2. Participant is intolerant of the study medication despite predetermined dose reductions and side effect management strategies
3. Safety concerns at the discretion of the investigator. These concerns will be documented in the source documents

Participants who discontinue treatment prematurely for the above reasons will be encouraged to remain in the post-treatment follow-up period for an additional 12 weeks, unless they withdraw consent. For those discontinued prematurely, blood samples will be obtained as listed for the week 48 end-of-treatment visit.

Patients who drop out after 6 months of treatment will be asked to undergo the liver biopsy. Those who drop out after fewer than 6 months of treatment or fail to undergo the follow up liver biopsy will be asked to undergo laboratory studies according to the follow up protocol.

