### Related to Medicinal Product

The phrase “**related to the medicinal product**” implies causality or attributability to Legalon®. An adverse event should be considered to be related to Legalon® in situations in which a causal relationship cannot be ruled out. As noted above, the clinical center PIs will assess the degree of relatedness of the study medications and adverse events (i.e., unrelated, possibly related, probably related, definitely related).

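### Section 3.4.4 allows an unmask request for any adverse event judged related, with no condition of severity or need to know, and the protocol's definition of related sets a low bar

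*Protocol*

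**What the plan says.** **Trigger.** Section 3.4.4 (Adverse event monitoring): "In the event that an investigator considers an adverse event to be related to study medication, the investigator may submit an unmask request". The request goes "to the clinical center investigational pharmacist to unmask the study drug dose, per the study specific unmasking procedure". That procedure is not part of the protocol text.

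**Meaning of related.** Section 7.5 (Related to Medicinal Product): "An adverse event should be considered to be related to Legalon® in situations in which a causal relationship cannot be ruled out". The investigator's scale is "unrelated, possibly related, probably related, definitely related". The protocol gives no other definition of relatedness.

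**What the investigator judges afterwards.** Section 2.3: "The primary outcome variable for safety is the occurrence of a dose-limiting toxicity during the 48-50 week treatment period". Under Section 3.4.2 the investigator has discretion over dose reduction for persistent grade 2 toxicity and over return to the earlier dose. Section 3.5 lists, among the reasons for stopping treatment, "Safety concerns at the discretion of the investigator".

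**After unmasking.** No section says that a participant whose assignment has been disclosed leaves treatment or passes to another assessor.

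**The concern.** In a double-masked trial the usual ground for opening the code is that someone must know the assignment to care for the participant or to meet a reporting duty. Here the stated ground is an opinion about causality. Because related means no more than that causality cannot be excluded, the opinion is easily reached for the symptoms that the Background (Silymarin) lists as reported effects, such as nausea, dyspepsia, bloating and headache.

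Safety is the first primary objective in Section 2.1. An investigator who knows the arm then grades later events, assigns relatedness and decides on discretionary reduction or stopping for that participant. Those judgements feed the primary safety outcome, which the body of the protocol does not define beyond its name. Knowledge of the arm can shift them in either direction.

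**Working it through.** **1. The rules side by side.**

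| Place | Condition | Consequence |
|---|---|---|
| 3.4.4, Adverse event monitoring | Event considered related | Unmask request may be made |
| 7.5, Related to Medicinal Product | Causality cannot be excluded | Event counts as related |
| 3.4.2 | Grade 1 toxicity | No dose reduction |
| 3.4.3, both tables | Moderate or severe event, reduced dose | Still 5 capsules per dose |
| 7.5, Adverse Events Requiring Expedited Reporting | Serious and related and unexpected (or any death) | Expedited report |

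A grade 1 event whose cause is uncertain meets the first two rows. It leads to no dose reduction under the third, and if it is not serious it falls outside the fifth. The fourth row shows that a reduction does not itself need the code, because active and placebo capsules are exchanged within a constant five. So the request rule reaches events for which the protocol's other rules call for no disclosure.

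**2. How sensitive the safety outcome is.** Inputs from Section 6.1: background toxicity rate 0.05, maximum tolerated rate 0.10. Arm size from Section 6.3: 40. Assumption: the toxicity rate in 6.1 is the rate of the Section 2.3 safety outcome.

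The plan's own figure first. For rates 0.05, 0.10 and 0.10 the mean is 0.0833, and the noncentrality is
40 × [(0.05 − 0.0833)² + 2 × (0.10 − 0.0833)²] / (0.0833 × 0.9167) = 40 × 0.001667 / 0.07639 = 0.873.
On 2 degrees of freedom at α = 0.05 this gives power of 12.1%, matching the stated 12%.

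Expected events per arm:
- at 0.05: 40 × 0.05 = 2
- at 0.10: 40 × 0.10 = 4
- one event judged differently moves an arm's rate by 1/40 = 2.5 percentage points
- two move it by 5 points, the whole distance from background to maximum tolerated rate

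This needs no assumption about how often unmasking occurs. It says only that few differently judged events are needed.

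**3. How many participants could be affected.** "A total of 120 subjects will be enrolled at the 4 clinical centers", so most would mean more than 60. The protocol gives no rate of related events. The nearest figures are:
- Phase I (Rationale for Dose Selection, High Dose): 2 of 12 on active drug had a mild event, 16.7% (exact 95% CI 2.1% to 48.4%). One was unrelated and one unlikely related.
- Counting only the second: 1 of 12, 8.3% (0.2% to 38.5%).

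Applied to 120, these point estimates give about 20 and about 10. As a range of assumed rates, 5%, 10%, 25%, 50% and 60% give 6, 12, 30, 60 and 72 participants. The documents do not pick out a value.

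**4. Reach to the NAS endpoint.** Under Section 3.5, those who stop before 6 months are not asked for a biopsy. Under Section 6.3, a participant who drops out with no follow-up biopsy counts as a failure. Purely as an illustration, let 5 of 40 leave early from one arm, with leavers otherwise responding at that arm's assumed rate:
- from placebo: 0.15 × 35/40 = 13.1%, a fall of 1.9 points, favouring silymarin
- from 700 mg: 0.55 × 35/40 = 48.1%, a fall of 6.9 points, against silymarin

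The planned differences from placebo are 40 − 15 = 25 and 55 − 15 = 40 points. The sign depends on who leaves, and the protocol gives no basis for choosing.

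**The case against.** **The text permits a request, not an unmasking.** The request is handled under a separate procedure that may add limits, a log and rules on who is told. This stands: the finding is about what may be requested, not about how often the code would be opened. It does not remove the point, since the only condition the protocol states is relatedness.

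**The definition of related belongs to regulatory reporting,** where a wide net is deliberate. That is true of its setting. But Section 3.4.4 uses the same term, and the protocol offers no narrower meaning.

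**A reader might infer that most participants could be unmasked.** The documents do not support this. No related-event rate is given. The Phase I counts and the low toxicity rate anticipated in Section 6.1 point to a minority, although 48-50 weeks of exposure could raise it.

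**A reader might infer that the primary efficacy result is biased in favour of silymarin.** This is not supported either. The study pathologist reads all slides at the end without knowing whose they are (Section 4.2, Liver biopsy), the protocol does not say that the participant is told the assignment, and early stopping could run either way. Nor does the text say that an unmasked investigator would adjust diabetes or lipid drugs.

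**The safety comparison is not a primary hypothesis, and severity follows CTCAE.** Both are correct and limit the damage. Dose-limiting toxicity is still the named primary safety outcome, and relatedness and discretionary actions are not fixed by a grading scale.

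**Conclusion.** The concern holds in a limited form. A rule that the protocol states, rather than a detail left to another document, lets a mild event of uncertain cause support an unmask request for a participant who stays on treatment and under the same investigator. That loss of masking is avoidable, because the protocol's own handling of grade 1 events and of dose reductions does not need the code.

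The exposure is mainly in dose-limiting toxicity, event grading, relatedness and discretionary stopping. Its importance comes from the small counts: about 2 against 4 events per arm of 40, if the Section 6.1 rates describe this outcome. The share of participants affected cannot be estimated. An effect on NAS through retention is possible but unquantified in size and direction. The unseen unmasking procedure may already narrow the rule; if so, the protocol should say the same. This is a cheap improvement, not a threat to the trial's validity.

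**What to change.** Amend Section 3.4.4 (Adverse event monitoring) so that:
- unmasking requires that knowledge of the assignment is needed for the participant's immediate care, or for expedited regulatory reporting with disclosure limited to those who file the report; relatedness alone is not enough
- the investigator records relatedness and toxicity grade before the code is opened
- each unmasking is logged with date, reason and who was told
- unmaskings are reported by arm

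Make the referenced unmasking procedure agree with this text. Dose handling stays with Sections 3.4.2 and 3.4.3 as they stand.

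The cost is a short amendment and a log. Investigators lose discretionary unmasking for minor events but keep access whenever care depends on it.
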